### Adverse events

We anticipate that the potential risk of this study is minimal. First, to minimize the risks of failure in performing surgeries under LPP, we will exclude patients with a history of pelvic procedures, which may lead to adhesions and may increase the manipulation difficulty. Furthermore, all five surgeons involved have at least 10 years of experience in performing laparoscopic surgeries. Second, SPP has been safely used in PUMCH for more than 20 years. Patients with severe liver, heart, lung and kidney dysfunction will be excluded; thus, the potential risk of irreversible ischemic organ injury caused by SPP should be extremely low. Third, rocuronium is mainly metabolized in the liver, and no evidence exists to show that the dosage used in deep NMB has renal toxicity in patients without ESRD. Finally, to avoid residual paralysis, 6 mg neostigmine will be given at the end of surgery to antagonize the residual muscle relaxant, and patients will not be extubated until the TOF ratio is > 90%.

Adverse events information will be collected spontaneously from the participants during the follow-up and recorded in CRFs with details (time, severity, treatment, outcome, and the relationship to the intervention). Serious adverse events will be reported to the medical ethics committee.

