### Participant selection

All patients scheduled for elective laparoscopic pelvic surgeries under general anesthesia will be screened for eligibility by an investigator who will not be involved in the process of randomization, intervention, data collection, or outcome assessment. Patients will be considered eligible if they meet the inclusion criteria and do not meet the exclusion criteria. Written informed consent will be obtained after evaluation.

The inclusion criteria are as follows:
Age 18–70 yearsAmerican Society of Anesthesiologist (ASA) Classification II-IIIDiagnosis of diabetes mellitusEstimated surgery duration > 3 h. The estimated surgery duration will be determined by the average duration of the same type of surgery by the same surgeon in the last year.

The exclusion criteria are as follows:
Not willing to participate in the study or unable to sign informed consentDiagnosis of any kidney diseases other than diabetic kidney diseasesSevere renal insufficiency defined as serum Cr > 2 times the upper limit of normal, urine output < 0.5 ml/kg/h, or estimated glomerular filtration rate (eGFR) < 60 ml/hSevere liver, lung or heart dysfunctionKnown or suspected neuromuscular diseaseUse of drugs that may affect neuromuscular block monitoringSevere diabetic neuropathy or any other peripheral neuropathyKnown or suspected allergy to general anestheticsFamily history of malignant hyperthermiaPrevious history of pelvic surgery

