### Outcome measures

The primary outcome is serum CysC level, which is a sensitive biomarker of renal injury, and this will be measured 30 min before pneumoperitoneum insufflation (T1), 30 min after pneumoperitoneum deflation (T2), 24 h postoperatively (T3), and 72 h postoperatively (T4). Among them, T1 will be the baseline. The mean difference of the serum CysC between groups will be used as the effect measure. We will compare the serum CysC between groups throughout T2, T3, and T4, using mixed-effect model which can provide an estimate for the overall effect in the whole timeframe.

The secondary outcomes include four indicators of renal function: (1) serum Cr level measured at T1, T2, T3, and T4; (2) intraoperative urine output; (3) the presence of erythrocytes in urinary sediment on postoperative days 1 and 3; and (4) renal tissue oxygen saturation measured every 15 min following pneumoperitoneum insufflation, and cerebral oxygen saturation will be used as an internal reference to adjust individualized differences. The other three secondary outcomes selected to evaluate surgical conditions are (1) surgical condition rating scale measured every 15 min starting from the introduction of the first trocar by five surgeons independently, (2) duration of surgery, and (3) the occurrence of bucking or body movement during the surgery. The details of the secondary outcomes are demonstrated in Table 3.

**Table 3 Tab3:** The secondary outcomes

Domain	Measurement	Metric	Aggregation	Time point
renal function	serum Cr level	difference between groups in the whole timeframe	mean	30 min before PP insufflation, 30 min after PP deflation, postoperative 24 h, and postoperative 72 h
renal function	intraoperative urine output	difference between groups	mean	NA
renal function	the presence of erythrocytes in urinary sediment	difference between groups	portion	postoperative day 1 and day 3
renal function	renal tissue oxygen saturation	difference between groups in the whole timeframe	mean	every 15 min since PP insufflation
surgical condition	surgical condition rating scale	difference between groups in the whole timeframe	median	every 15 min starting from the introduction of the first trocar
surgical condition	duration of surgery	difference between groups	mean	NA
surgical condition	the occurrence of bucking or body movement during surgery	difference between groups	portion	NA

*Abbreviations*: *NA* not applicable, *PP* pneumoperitoneum

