### Data collection

The following demographic data and previous medical history will be collected by a data collector preoperatively from the medical records: sex, age, height, weight, duration of diabetes, and the presence of any complications of diabetes.

Peripheral venous blood samples will be extracted at T1, T2, T3, and T4, and urine samples will be obtained on the morning of postoperative days 1 and 3. The samples will be sent immediately to the clinical laboratory in PUMCH and will be analyzed by the staff there. Blood samples will be centrifuged at room temperature to obtain serum. Serum CysC concentration will be determined by sandwich enzyme-linked immunosorbent assay (ELISA), and Cr will be measured using an enzymatic method. Urine samples will be analyzed by automated urine microscopy analysis. All the samples will be handled within one hour since their arrival at the laboratory. We do not plan to store the samples after the study.

During the surgery, in addition to the secondary outcomes, two data collectors will record the heart rate, ABP, SV, and SVV every 15 min. They will also record the amount of crystalloid and colloid infused, the amount of transfusions, and the estimated blood loss.

There is an anesthesiologist and a surgeon in charge of monitoring the adherence to the protocol. Any suspected nonadherence during participant recruitment, randomization, intervention, data collection, or outcome assessment will be recorded. Based on the intention-to-treat (ITT) principle, all the randomized participants will be analyzed, despite any nonadherence to the protocol.

Data will be collected in the paper-based case report form (CRF) and then entered into a digital database by two independent investigators. Each patient will be distinguished by a unique serial number, and his or her name will be concealed. The database will be secured by a password, which will be restricted to the Data Safety Monitoring Committee (DMC), which is composed of two anesthesiologists with more than 10 years of experience. They will check the completeness and accuracy of the data, and the auditing will be independent from that of the other investigators. The information recorded in medical charts and saved in monitors will be traced to correct and supplement the data. The database will be locked up after the entry of the last case. The allocation will not be unblinded until all data analysis is completed; thus, the data analyst will also be blinded.

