## Discussion

To the best of our knowledge, this is the first trial to date assessing the effects of pneumoperitoneum pressure and NMB on postoperative renal function in diabetes patients. Accumulating evidence shows the benefits of combined LPP and deep NMB in reducing postoperative pain and enhancing recovery [28, 34]. However, several other studies have found negative results [41, 42]. Furthermore, previous research did not focus on renal function or diabetes patients. Considering the increasing prevalence of diabetes and the poor prognosis of renal complications, our study can provide important evidence on intraoperative renal protection in this high-risk population. Another strength of this study is that we plan to evaluate renal function using multiple biomarkers, including CysC and Cr levels, erythrocytes in urinary sediment, intraoperative urine output, and renal tissue oxygen saturation. We anticipate that their sensitivity will allow us to detect small changes in renal function. Furthermore, we will collect data on other intraoperative factors that may affect renal perfusion, such as hemodynamic indices and infused fluid, so we can test their balance and adjust potential confounding effects if necessary.

Our study is limited by the following aspects. First, we will exclude patients with ASA IV or with severe organ dysfunction; thus, the conclusion of this study cannot be generalized to critical cases. Second, since the surgeons involved in this study are experienced in laparoscopic procedures, they may have lower requirements for pneumoperitoneum pressure. Third, for the concern of workload, the diagnosis of diabetes will be based on the patients’ medical records rather than the “gold criteria,” the oral glucose tolerance test (OGTT). Therefore, some patients with undiagnosed early diabetes may be inadvertently excluded. Finally, unexpected events may occur, such as an actual surgery duration > 3 h or conversion to open surgery. Based on the ITT principle, the data of these cases should also be collected and analyzed. Considering the equal likelihood of the occurrence of non-adherence in each group, the effect on the results should be low.

In conclusion, our study will investigate the effects of LPP and deep NMB on postoperative renal function and surgical conditions. We hope this study can shed light on intraoperative renal protection in diabetes patients receiving laparoscopic surgeries.

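### The one stated route for adverse events, spontaneous reports by participants during follow-up, suits intraoperative and emergence harms poorly, and several of these have no staff-recorded count by arm

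*Protocol article*

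**What the plan says.** The Adverse events section of the protocol article sets the source, the mode and the window in one sentence: "Adverse events information will be collected spontaneously from the participants during the follow-up". The case report form entry covers timing, severity, management, outcome and relation to the intervention. The section then adds: "Serious adverse events will be reported to the medical ethics committee". It does not say how a serious event comes to be detected.

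The same section names risks of the interventions. Patients with earlier pelvic procedures are excluded "to minimize the risks of failure in performing surgeries under LPP". Ischemic organ injury and residual paralysis are also mentioned. The Discussion lists "conversion to open surgery" among unexpected events.

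Outside that section, staff record a good deal during the operation. Under Data collection, "two data collectors will record the heart rate, ABP, SV, and SVV every 15 min", and they also note fluids, transfusion and estimated blood loss. One of the secondary outcomes under Outcome measures is "the occurrence of bucking or body movement during the surgery".

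**The concern.** The adverse event sentence is a stated method, not a detail left for a fuller document, and it fits these interventions badly. The Participant selection section fixes the setting: "All patients scheduled for elective laparoscopic pelvic surgeries under general anesthesia will be screened". Pneumoperitoneum pressure and depth of block act while the patient is unconscious. A patient is poorly placed to volunteer an organ or vessel injury, or to know that the operation could not go on at the assigned pressure.

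At stake is the balance of benefit and harm. If low pressure or deep block shows a renal or surgical-field advantage, a reader will want operative and emergence harms set beside it, by arm. If some of those harms are picked up only haphazardly, their absolute differences between arms will tend to look smaller than they are, which flatters whichever arm has more of them.

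**Working it through.** No figure in the plan bears on this point, so the check is one of reading. For each kind of event that pressure or block depth could plausibly affect, I looked for a stated staff record and a stated comparison between groups.

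| Event | Staff record stated? | Comparison by arm stated? |
|---|---|---|
| Poor or unworkable surgical view | Yes. Rated every 15 min, with extra ratings on sudden worsening (Surgical condition rating) | Yes, secondary outcome |
| Bucking or movement | Yes (Outcome measures) | Yes, secondary outcome |
| Prolonged surgery | Yes (Outcome measures) | Yes, secondary outcome |
| Hemodynamic change, blood loss, transfusion | Yes (Data collection) | Summarized as intraoperative factors (statistical analysis section); the Discussion foresees testing their balance. Not treated as safety data |
| Departure from protocol | Yes. Suspected nonadherence is recorded (Data collection) | Enters a sensitivity analysis; no count by arm stated |
| Conversion to open surgery | Discussion says data of such cases should be collected and analyzed | Not an outcome in Table 3; no count by arm stated |
| Surgery unable to proceed at the assigned range | No dedicated entry; could surface as a very low rating or as nonadherence | None stated |
| Visceral or vascular injury | None stated | None stated |
| Residual weakness or reintubation | Train-of-four ratio checked before extubation; nothing stated for afterwards | None stated |

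Three further passages decide how far the lower rows are covered.

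1. **The Discussion on conversion.** In context, the sentence keeps converted patients in the intention-to-treat analysis. It does not make conversion an event to be tallied. The Discussion then treats nonadherence as equally likely in every group. Yet the Background says that low pressure reduces the working space, which is a reason to expect operative difficulty to differ by pressure. A count by arm would test that assumption.
2. **The monitoring committee.** Data collection gives it the task of checking completeness and accuracy. No safety review is described that would supply the missing events.
3. **Charts and monitors.** Data collection says these records are used to correct and supplement the data. Some events could be recovered this way, but with no field on the form to supplement, recovery would depend on chance.

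The upper five rows are recorded by staff. The last four rows lack a stated record, a stated count by arm, or both.

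**The case against.** The strongest reply has four parts.

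- **The sentence does not exclude other sources.** It nowhere restricts adverse events to participant reports. Serious events are not tied to them, and an entry on severity and relation to the intervention implies staff judgment. A journal article also commonly leaves the event form to the full protocol. This stands in part. A reader might infer that participants are the sole source; the text does not say so. It is still the one route stated, and it names a passive method.
- **Staff already capture many of the relevant harms.** This stands. A reader might infer that the harms most likely to differ by pressure or block would go unseen. That is not supported: view, bucking, duration, hemodynamics, blood loss and transfusion are all recorded during surgery, suspected nonadherence is logged, and data on conversions are to be collected.
- **Patients can report some of these events.** A patient will learn afterwards of an open operation and stays on the ward for at least 3 days. This stands for conversion, and perhaps for weakness that persists. It does not extend to events known only to the operating team.
- **The hypothesis does not rest on adverse event reports.** The Abstract claims renal protection without loss of surgical view, and the Leiden rating tests the second part. This stands. A reader might infer that the trial means to prove safety from an absence of volunteered events; it states no such plan.

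**Conclusion.** The point holds in a limited form. The stated adverse event method is passive, relies on participants and falls in follow-up, whereas the interventions act under anesthesia. Four kinds of event are left without a full staff record and count by arm: conversion to open surgery (data to be collected, but no tally set up), visceral or vascular injury, surgery unable to proceed at the assigned pressure range, and residual weakness or reintubation.

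The size cannot be put in numbers. The documents give no rates for these events and no reporting fraction, so any estimate of events lost would be invented. The primary outcome, the listed secondary outcomes and the sample size are untouched. The consequence is confined to how completely harms can be compared between arms.

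The conclusion assumes that the published sentence reflects the working procedure. If the full protocol or the case report form already has a staff-completed complication list, the article's wording needs correcting but the conduct does not. That these harms arise mainly during surgery or emergence is an inference from when the interventions act, not a figure in the protocol. The change is worth making because it is cheap and replaces a weak stated method with a concrete one.

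**What to change.** Change the adverse event sentence so that ascertainment is active and staff-recorded:

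1. **End of surgery.** The blinded data collectors already in the operating room complete a fixed list for every patient: conversion to open surgery, surgery unable to proceed at the assigned pressure range, and visceral or vascular injury. The second item can be a yes/no answer relayed by the nurse who holds the allocation, so that the collectors do not learn the pressure.
2. **Before discharge from recovery.** They record residual weakness and reintubation as present or absent.
3. **24 h (T3) and 72 h (T4).** Participants are asked a short checklist at these contacts, when blood is drawn anyway. Spontaneous reports continue to be accepted.
4. **Reporting.** Tabulate these events by factor (pressure, block depth) and by the four groups, together with the blood loss, transfusion and bucking data already collected. State that serious events may come from any of these sources.

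This changes what is recorded, not how any patient is treated. The cost is a few case report form fields, collectors following patients into recovery, and more recorded events to enter and classify.

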## Discussion

To the best of our knowledge, this is the first trial to date assessing the effects of pneumoperitoneum pressure and NMB on postoperative renal function in diabetes patients. Accumulating evidence shows the benefits of combined LPP and deep NMB in reducing postoperative pain and enhancing recovery [28, 34]. However, several other studies have found negative results [41, 42]. Furthermore, previous research did not focus on renal function or diabetes patients. Considering the increasing prevalence of diabetes and the poor prognosis of renal complications, our study can provide important evidence on intraoperative renal protection in this high-risk population. Another strength of this study is that we plan to evaluate renal function using multiple biomarkers, including CysC and Cr levels, erythrocytes in urinary sediment, intraoperative urine output, and renal tissue oxygen saturation. We anticipate that their sensitivity will allow us to detect small changes in renal function. Furthermore, we will collect data on other intraoperative factors that may affect renal perfusion, such as hemodynamic indices and infused fluid, so we can test their balance and adjust potential confounding effects if necessary.

Our study is limited by the following aspects. First, we will exclude patients with ASA IV or with severe organ dysfunction; thus, the conclusion of this study cannot be generalized to critical cases. Second, since the surgeons involved in this study are experienced in laparoscopic procedures, they may have lower requirements for pneumoperitoneum pressure. Third, for the concern of workload, the diagnosis of diabetes will be based on the patients’ medical records rather than the “gold criteria,” the oral glucose tolerance test (OGTT). Therefore, some patients with undiagnosed early diabetes may be inadvertently excluded. Finally, unexpected events may occur, such as an actual surgery duration > 3 h or conversion to open surgery. Based on the ITT principle, the data of these cases should also be collected and analyzed. Considering the equal likelihood of the occurrence of non-adherence in each group, the effect on the results should be low.

In conclusion, our study will investigate the effects of LPP and deep NMB on postoperative renal function and surgical conditions. We hope this study can shed light on intraoperative renal protection in diabetes patients receiving laparoscopic surgeries.

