Patients undergoing abdominal surgery are more likely to develop AKI than those undergoing other noncardiac, nonvascular surgeries [12, 18]. Pneumoperitoneum is necessary for better visualization and manipulation in laparoscopic surgery. The increased intra-abdominal pressure (IAP) induced by pneumoperitoneum can activate the renin-angiotensin-aldosterone system (RAAS) and cause renal vascular and parenchymal compression [19], which will further undermine renal perfusion and create ischemic insults [20]. Prior literature has demonstrated the association between increased IAP and AKI in critically ill patients after abdominal surgery [21, 22]. Intraoperative oliguria and diminished glomerular filtration rates have also been observed [23]. These changes deteriorate with increases in pressure and extended durations [23]. However, several studies have reported conflicting results, indicating that laparoscopic surgery does not carry an additional risk of postoperative AKI [24–26]. Therefore, high-quality evidence is needed for a better understanding.

Low-pressure pneumoperitoneum (LPP, 7–10 mmHg) is recommended to minimize the ischemic organ injury caused by standard-pressure pneumoperitoneum (SPP, 12–15 mmHg) [27]. LPP has been successfully used in a series of abdominal and pelvic surgeries, such as laparoscopic hysterectomy, cholecystectomy, and adrenalectomy [28–31]. However, LPP compromises the working space and surgical field, leading to prolonged surgical durations [32]. Fortunately, studies have shown that deep neuromuscular blockade (NMB) can ameliorate this issue [33, 34] and facilitate the use of LPP [35–37]. However, such effects are still controversial [38, 39]; thus, further studies are still required.

Therefore, the objective of this study is to assess the effect of LPP *versus* SPP on renal function protection in patients with diabetes undergoing laparoscopic pelvic surgery and to evaluate whether deep NMB can improve surgical conditions compared with moderate NMB. We hypothesize that the use of LPP, facilitated by deep NMB, can improve postoperative renal function after laparoscopic pelvic surgeries.

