### Interventions

#### Anesthesia

An intravenous (IV) cannula will be inserted for the administration of anesthetic drugs. All enrolled patients will receive total intravenous anesthesia (TIVA). Intraoperative monitoring will include electrocardiography (ECG), pulse oximetry (SpO_2_), invasive arterial blood pressure (ABP), stroke volume (SV) and stroke volume variation (SVV) measured by LiDCO-rapid™, inspiratory and expiratory gas analysis, pressure of end tidal carbon dioxide (PetCO_2_), tidal volume, airway pressure, bispectral index (BIS), cerebral oxygen saturation, renal tissue oxygen saturation, nasopharyngeal temperature, and peripheral skin temperature. Anesthesia will be induced via the target-controlled infusion (TCI) of propofol (at an effect-site concentration of 6 μg/ml) and a bolus injection of 2–3 μg/kg fentanyl or 0.2–0.3 μg/kg sufentanil. Endotracheal intubation will be performed after the administration of a predefined dose of rocuronium based on the grouping. Anesthesia will be maintained with a TCI of propofol and continuous infusion of remifentanil. Mean blood pressure and heart rate fluctuations will be maintained within 20% of baseline, and the targeted BIS value will be 50–60. Fluid infusion will be adjusted to maintain SV < 10% and SVV < 13. Patients will be mechanically ventilated using a volume-controlled pattern with a tidal volume of 7–9 ml/kg and a frequency of 10–13/min. PetCO_2_ will be maintained between 35 and 45 mmHg. Forced-air warming will be used to maintain central and peripheral skin temperatures ≥ 36 °C and 32 °C, respectively.

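### The Discussion leaves room to adjust treatment comparisons for intraoperative haemodynamics and infused fluid, which are measured after randomization and are not confounders of a randomized comparison

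*Protocol article*

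**What the plan says.** The Discussion explains that further influences on kidney perfusion during the operation will be recorded, and gives examples and the purpose: "such as hemodynamic indices and infused fluid, so we can test their balance and adjust potential confounding effects if necessary".

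Data collection fixes when these are measured: during the operation, "two data collectors will record the heart rate, ABP, SV, and SVV every 15 min". Fluid volumes are covered in the same place: "They will also record the amount of crystalloid and colloid infused", along with transfusions and blood loss. Randomization and blinding places allocation after enrollment and immediately before surgery.

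Sample size calculation and statistical analysis gives a different covariate rule. Variables found unbalanced at baseline enter the ANOVA or mixed-effects model. Intraoperative factors appear there only as something to be described. The legend of Table 1 marks baseline variables and intraoperative factors as separate classes.

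For one secondary outcome, renal tissue oxygen saturation, Outcome measures adds that "cerebral oxygen saturation will be used as an internal reference to adjust individualized differences".

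**The concern.** A confounder of a treatment comparison must come before treatment. Randomization deals with those variables up to chance. Blood pressure, stroke volume and its variation, and fluid volume during surgery arise after allocation and largely under the assigned pressure and block. The Background describes pressure acting through renal perfusion, "which will further undermine renal perfusion and create ischemic insults", and the Discussion picks these covariates because they may affect renal perfusion. On the article's own reasoning they are candidate mediators.

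A balance test followed by adjustment is then triggered most readily when the intervention has shifted the variable. The adjusted estimate no longer answers the stated objective, which is the effect of low versus standard pressure on renal function. Conditioning on a post-randomization variable can also open a non-causal path through unmeasured causes shared with the outcome. The Discussion gives no threshold, model or outcome for the adjustment, so the choice could be made after seeing the data.

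**Working it through.** **1. Timing.** Allocation comes just before surgery. The group-specific rocuronium dose follows at induction (Neuromuscular block monitoring and management), then insufflation at the assigned pressure. Haemodynamics are recorded every 15 min during surgery, and fluid is an intraoperative total. Both therefore follow randomization. Readings taken under the block and the pneumoperitoneum follow the start of both interventions.

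**2. Can treatment affect them?** Anesthesia states "Fluid infusion will be adjusted to maintain SV < 10% and SVV < 13", so fluid volume responds to intraoperative haemodynamics. It also states "Mean blood pressure and heart rate fluctuations will be maintained within 20% of baseline". That band limits a between-arm difference in blood pressure and heart rate but does not remove it.

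**3. The two covariate rules side by side.**

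| Section | Baseline variables | Intraoperative factors |
|---|---|---|
| Sample size calculation and statistical analysis | Into the model if unbalanced | Described |
| Discussion | Not addressed | Balance tested, adjusted for if judged necessary |

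Table 1 separates the two classes, so baseline in the statistical section cannot be stretched to cover intraoperative factors. The rules conflict.

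**4. The plan's own sample size.** Inputs from the statistical section: difference 0.05 mg/dl, SD 0.186 mg/dl, two-sided 5%, 90% power.

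n per margin = 2 × (1.960 + 1.282)² × 0.186² / 0.05² = 290.8, rounded up to 291, so 582 in total. This matches. With 10% dropout, 582 / 0.9 = 646.7, so 647, or 648 for four equal groups. This also matches.

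**5. Illustration of the stakes.** Let m be the share of the effect that passes through the covariates. The document does not give m, so it is assumed. The adjusted model targets 0.05 × (1 − m). With the SD unchanged, the standard error is 0.186 × √(2/291) = 0.01542, and power = Φ(0.05 × (1 − m) / 0.01542 − 1.960).

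| m (assumed) | Adjusted target, mg/dl | Power |
|---|---|---|
| 0% | 0.0500 | 90% |
| 10% | 0.0450 | 83% |
| 25% | 0.0375 | 68% |
| 50% | 0.0250 | 37% |

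A regression simulation (2000 runs per setting, 291 per margin, covariate shifted by half its SD between arms) gave mean adjusted estimates of 0.045, 0.040, 0.035 and 0.025 for m = 10, 20, 30 and 50%. Rejection rates were 80, 72, 61 and 38%. The unadjusted estimate stayed at 0.050. The simulated rate at 10% is slightly below the formula because a covariate related to treatment inflates the standard error. Arm explains 0.0625 / 1.0625 = 5.9% of the covariate's variance, so the inflation is 1 / √(1 − 0.059) = 1.03.

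**6. Direction.** The table covers mediation in the same direction as the total effect. If extra fluid partly offsets a harm of higher pressure, m is negative. At m = −10%, for example, the adjusted target would be 0.05 × 1.10 = 0.055 mg/dl, further from the null than the total effect.

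**The case against.** The strongest reply is that the statistical section governs. It admits only baseline variables to the models and describes intraoperative factors, which is most of the remedy. The other sentence is a Discussion remark about strengths, qualified by an if, with no model attached. A reader might infer that the primary cystatin C analysis will be adjusted for haemodynamics and fluid. The article does not say so, and that part of the reply stands. What remains is that the Discussion names these variables as potential confounders and states an intention to adjust where needed, so the document gives two rules for the same class of variable.

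A second reply is that the mechanism in the Background is hormonal activation and compression of the renal vessels and parenchyma. Systemic blood pressure, stroke volume and fluid are not named as mediators, and the anaesthetic protocol holds some of them in a band. This also stands: mediation is plausible but not established, and its share could be near zero. It does not make these variables confounders.

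A reader might also infer that adjustment necessarily shrinks the effect. With fluid titrated to haemodynamics, and with possible unmeasured common causes, the direction is not fixed.

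Finally, a reader might extend the same criticism to cerebral saturation. The article uses it for one secondary outcome only. It does not say whether the reference is concurrent or a baseline value, or that treatment changes it. That part is a caution and does not touch the primary outcome.

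**Conclusion.** The point holds in limited form. The Discussion permits, conditionally and without a stated trigger, adjustment of treatment comparisons for variables measured after randomization that treatment may affect. That would not estimate the total effect of either factor, and it contradicts the covariate rule in the statistical section. It should be corrected before the data are analysed.

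The size of any bias cannot be derived from the document. The fall in power from 90% to 83, 68 or 37% rests on assumed mediated shares of 10, 25 and 50%, on mediation in the same direction as the total effect, and on an unchanged SD. At a share of zero nothing is lost. If the statistical section is followed as written, the planned 582 patients and 90% power are untouched by this point.

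The cut-off also needs care. A reader might take insufflation as the boundary between pre- and post-intervention measurements. That works for pressure but not for block depth, where the groups already differ from the rocuronium dose at induction.

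**What to change.** - Delete the adjustment clause from the Discussion. State in the statistical section that all efficacy comparisons, primary and secondary, adjust only for pre-intervention covariates, including T1 cystatin C. T1 is set at 30 min before insufflation, and the article does not say whether that is before the rocuronium dose. State which it is, and if it is after, say why T1 still serves as baseline for the block-depth comparison.
- Report intraoperative haemodynamics, fluids and blood loss descriptively by arm.
- Label any model containing them as exploratory, for example a mediation analysis.
- For renal tissue oxygen saturation, report the result without a cerebral reference, or referenced to readings taken before the first group-specific intervention. That means before the rocuronium dose, not merely before insufflation. Concurrent cerebral values may themselves be affected by treatment.

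The cost is a few sentences of wording and, if a reference is kept, one early reading from monitoring the protocol already lists. The sample size does not change.
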